***Methods and procedures***

Design: A multicentre, randomized, controlled phase III study will be conducted in 3 study sites in Sweden (Stockholm, Gothenburg and Umeå).

Study design and protocol will follow the CONSORT standards and are in accordance with the principles of the Declaration of Helsinki and Good Clinical Practice. The study protocol will be approved by the ethical committee in Stockholm and will be submitted for publication on *clinicaltrials.gov.*

Study Endpoints

The primary aim of the study is to compare the effectiveness of a) intensive training with HAL, b) intensive training without HAL and c) standard training, in a later phase (1-10 years) after stroke on independence in ambulation after intervention by comparing the Functional Ambulation Category in each group.

Secondary aims comprise the effectiveness of training with HAL on independence gait function and quality, cardiovascular function, activity of daily living and participation assessed at the end of intervention and at a 6 and 12 months follow-up. Effects on health care consumption during 12 months after the intervention will be explored and treatment related adverse events during the study will be documented. Further, associations between range of movement, strength and spasticity versus HAL mediated recovery will also be explored.

Setting: Setting: The study will be performed simultaneously at Danderyd University Hospital and Department of Clinical Sciences, Karolinska Institutet in Stockholm; Sahlgrenska University Hospital and University of Gothenburg in Gothenburg; Norrland University Hospital and Umeå University in Umeå.

*Recruitment of patients*

Eligible are persons, aged 18-70 years, recruited from out-patient rehabilitation units where they have passed a regular rehabilitation program due to stroke related hemiparesis/central paresis of the lower extremity (LE) after an ischemic or haemorrhagic first ever stroke (assessed by a stroke physician and verified by CT or MRI examination- this data will be collected from initial referral to the unit or in case of missing data, by contacting the physician or the medical records after approval by the study participant).

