All data collection will follow and be documented in individual Case Report Forms (CRF).

The HAL-training in Study I and II will documented in a standardized protocol, developed and tested in previous and ongoing studies. Conventional gait training in Study I will be documented based on data collected from medical records at the rehabilitation units.

Intensive gait training with and without HAL in Study II will be documented according to preformed forms. The participants in the 2d control group in who are not receiving an intervention, will document any scheduled training sessions in an web based application (app) or will be interviewed once a week according to a standardized protocol.

*Assessments*

Assessments will be made with valid instruments (not referenced in detail here) and performed once at baseline, immediately after the intervention period and at 6 and 12 months after the intervention period by a senior physician specialist physician, and by a blinded, experienced physiotherapist. The time points for the assessments are presented in the Table.

*Screening of function and disability:*

Data on Stroke type and localization will be collected from the medical records at the study sites. Body function will be assessed by use of the NIH Stroke Scale (NIHSS), mental function with Montreal Cognitive Assessment, executive function with the questionnaire Dysexecutive Questionnaire included in BADS (Behavioural Assessment of the Dysexecutive Syndrome), anxiety and depression with the Hospital Anxiety and Depression Scale and activity and participation by means of the Barthel Index and Modified Rankin Scale.

*Primary outcome measure*

The primary outcome will be the Functional Ambulation Categories (Holden 1984) that assesses activity in terms of independence in walking.

*Secondary outcome measures:*

Body function in terms of sensory function, pain and control of voluntary movement will be assessed with the Fugl Meyer Scale (FM-LE) and spasticity in the lower extremities with the Modified Ashworth Scale and the neuroflexor module and range of movement with the goniometer. Gait pattern function and walking will be assessed in laboratory gait analyses.

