Activities and Participation in terms of walking will be tested with the 10 meter walk test, 2 and 6 minutes’ walk test combined with the Borg RPE scale for endurance, the accelerometer SenseWear Pro2 will be used to assess energy expenditure and physical activity (number of steps) in everyday life balance in activity with the Berg Balance Scale, and perceived functioning and disability with the Stroke Impact Scale (SIS).

Qualitative evaluation based on interviews will be performed in subgroups. Treatment related adverse events will be documented.

Data on registered health care and rehabilitation utilization during 12 months after the intervention period will be retrieved from the local County Councils at the study sites.

*Other assessments*

Resistance to passive stretch of lower leg muscles (spasticity) by use of new Neuroflexor/foot module - for exploratory analyses of prediction.

HbA1c (long- term blood glucose level), plasma lipid profile, Blood pressure (over day curve); oxygen uptake for assessment of energy expenditure (performed in subgroup only); Body Mass Index; drug use – pharmacological, including antidepressants, smoking and alcohol will be documented.

*Power calculation and statistics*

Power calculation is based on previous studies of motor function after stroke and of the effects of training with HAL. Using FAC as the primary outcome measure and the expected minimum difference of one category between treatment groups, a significance level of 5% and a power of 80%, and an expected minimal loss of patients per treatment arm,

The study will require 54 (18x3) patients at each study sight, i.e. 162 patients in total.

Populations to be used for statistical analyses:

(1) All Available-Patients (AAP) population - all randomised patients regardless of further participation will be used to present demographic and baseline characteristics.

(2) Intent-to-Treat (ITT) population - all patients, who were randomised and started the intervention program regardless if and when they withdrew, will be used to present all efficacy and safety data.

Hypothesis testing will be carried out at the 5% (two-sided) significance level, descriptive summary statistics presented for continuous variables (median, minimum and maximum, arithmetic mean, 95% confidence intervals (CI), standard deviation (SD), standard error).

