In non-parametric analyses, the minimum, maximum, median, 5th, 25th, 75th, and 95th percentiles will be calculated. The median difference between treatment groups and the corresponding 95% CI will be presented as statistical analysis outputs. For categorical variables, counts and percentages will be presented, and comparison of intervention groups by use of generalised linear models to provide odds ratios (ORs), corresponding 95% CI and p-values< 0.05. For secondary endpoints we will use mixed models to explore change between and within groups over time.

Adverse events during the study period adverse events (such as falls, skin impact, pain during training session with HAL; new stroke or other cardiovascular events etc.)

will be documented according to a preformed protocol and their association or not to the Interventions will be classified by an external partner. Prevention of these will be standardised over study sites.

*Recruitment period*

Inclusion of patients will be ongoing from September 2015 – October 2017 with follow ups completed in November 2018.

*Limitations, potential bias*

Patients will be recruited from out-patient clinics which enables a recruitment of patients that have been assessed and found to be in need of rehabilitation interventions in the long-term phase after stroke. By using this procedure we will not be able to recruit patients who have not received rehabilitation interventions in out-patient care However, given the access to out-patient rehabilitation units in Stockholm we consider the risk of missing patients who meets the inclusion exclusion critera to be small. Thus, the study samples will represent those with needs of and probably with the greatest potential benefits from improved rehabilitation interventions. Based on our prior experiences, there might be a risk for an uneven gender distribution with more male than female. The reason for this is not clear but women tend to suffer a stroke later in life compared to men. Efforts will be made to avoid a bias in this respect.

*Generalisability*

Regarding the multicentre design, recruitment process and sample size, we expect the findings to be generalisable to the stroke population at focus (see limitiations)

*Funding*

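### The planned County Council extract does not depend on visit attendance and covers the 12 months after training, but it is assigned only to utilisation and cost, not to finding the strokes, cardiovascular events and fall injuries the protocol undertakes to document

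*Protocol*

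**What the plan says.** All places are in the Protocol under Methods and procedures unless stated otherwise.

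- **Commitment (Power calculation and statistics, adverse events paragraph).** The scope is "Adverse events during the study period adverse events (such as falls, skin impact, pain during training session with HAL", and the list goes on to "new stroke or other cardiovascular events etc". These "will be documented according to a preformed protocol and their association or not to the Interventions will be classified by an external partner". No window narrower than the study period is given.
- **Narrower scope elsewhere.** Study Endpoints says "treatment related adverse events during the study will be documented". Secondary outcome measures says "Treatment related adverse events will be documented".
- **Scheduled assessments (Assessments).** They are "performed once at baseline, immediately after the intervention period and at 6 and 12 months after the intervention period".
- **Register data (Secondary outcome measures).** "Data on registered health care and rehabilitation utilization during 12 months after the intervention period will be retrieved from the local County Councils". The purposes given for health care data, in Purpose and aims and in Study Endpoints, are utilisation, consumption and cost effectiveness. The Time plan places their collection between October 2016 and November 2018. No section links them to adverse events.
- **Safety population (Power calculation and statistics).** Safety data are presented for patients who were randomised and started the intervention program. Under Interventions, the second control group receives none.

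**The concern.** The protocol names grave events and promises to document them over the whole study, but it describes close contact in the training arms only for the 6 weeks of training. If events in the following year are collected at the 6- and 12-month assessments, capture depends on attendance, and attendance can depend on the event. A patient who has died, been readmitted or been disabled by a new stroke is less likely to come, and minor events several months back are easily forgotten.

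At stake is the credibility of the safety comparison in a phase III trial. With 54 patients per arm, serious events are likely to be few, so each missed one counts. The protocol also cites secondary stroke prevention as part of its rationale, so readers will look for recurrent events. A source that could supply many of them is already planned. Unless its content is specified before the data are requested, the diagnoses may never be extracted, and a later analysis plan cannot recover them.

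**Working it through.** The protocol gives no event rate or safety figure to reproduce, so the check is a timeline, a comparison of texts and a bounding illustration.

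**1. Share of follow-up after training.** Inputs: 6 weeks of training (Interventions) and 12 months of follow-up (Assessments), taken as 52 weeks.
- Total: 6 + 52 = 58 weeks.
- Share after training: 52 / 58 = 0.897, about 90%.
- All-arm assessments named in those 52 weeks: two, about 26 weeks apart.

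**2. Other contacts the text mentions.**
- HAL arm: one or two home visits at the end of the 6 weeks, for education.
- Second control group: an app log or weekly interview about scheduled training sessions, with no stated end.
- Subgroups: qualitative interviews, with no stated timing.

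None is described as a safety contact, and none covers all three arms.

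**3. Can the undercount be sized?** Only on assumptions that the documents do not supply. Let r be the 12-month risk of a new stroke or other cardiovascular event, and m the share of affected patients who do not return and are not otherwise traced. Expected missed events = 162 × r × m.

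| r (assumed) | Events in 162 | Events per arm of 54 | Missed, m = 10% | Missed, m = 50% |
|---|---|---|---|---|
| 2% | 3.2 | 1.1 | 0.3 | 1.6 |
| 5% | 8.1 | 2.7 | 0.8 | 4.0 |
| 10% | 16.2 | 5.4 | 1.6 | 8.1 |

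The result runs from 0.3 to 8.1 events. The share missed is simply m, which is assumed. The table shows that the size is undetermined; it does not estimate it.

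**4. Scope of adverse events.** Under the adverse events paragraph, a stroke in any arm is recorded first and its relatedness is judged afterwards. Under Study Endpoints and Secondary outcome measures, only treatment-related events are documented. On that narrower wording the no-intervention arm would contribute essentially nothing, so the arms could not be compared.

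**5. Denominator.** The safety population requires having started the intervention program. Which patients in the no-intervention arm meet that condition is unclear.

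**6. Calendar.** Inclusion runs to October 2017. Assume training starts on the day of inclusion.
- Included 1 October 2017: training ends 12 November 2017, and 12 months end 12 November 2018.
- Included 31 October 2017: training ends 12 December 2017, and 12 months end 12 December 2018.
- Latest inclusion whose 12 months end by 30 November 2018: 30 November 2017 minus 42 days = 19 October 2017.

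Patients included after 19 October 2017 therefore have windows running past the stated end of both follow-up and utilisation data collection. Any delay between inclusion and start of training moves this cut-off earlier.

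**The case against.** The strongest objection is that the gap is read from silence. Adverse events are to be documented under a separate preformed protocol that is not shown and may provide for interim contacts, record review or reports from relatives. The table of assessment time points is not in the text at hand either. The document nowhere says that adverse events are collected only at visits, or that register data will be kept out of the safety evaluation. This stands. A reader might infer that patients have no contact at all between visits, or that the register data are deliberately excluded from safety; the text supports neither.

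It is also fair that a missed visit is not always a missed event, since a site may learn of a death or admission when it tries to book the visit, and the sample size paragraph expects minimal loss. On the narrower treatment-related wording, a stroke months after training is largely outside the stated scope. Recurrent stroke is not an endpoint, and a handful of events per arm would say little about prevention. Nothing in the document shows that trained patients fall more at home.

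What remains is that the protocol makes a commitment covering the whole study, names only two all-arm assessments for the last 52 weeks, and gives its one attendance-independent source no safety role. The unseen adverse event protocol might close the gap. Even then, the content of the extract and the conflict over scope must be settled in the main protocol.

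**Conclusion.** The point holds as an inexpensive improvement, together with two inconsistencies to reconcile. About 90% of each patient's observation time has only two named all-arm assessments, and serious events may themselves prevent attendance, so visit-based capture can undercount them. The planned register data cover the same 12 months without depending on attendance but are assigned only to utilisation and cost.

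A reader might go further and state what fraction of events in an arm would be lost. The documents do not support that: they give neither an event rate nor a non-return rate, and any percentage would reflect the values chosen.

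The conclusion rests on three assumptions: that the unseen adverse event protocol does not already provide an equivalent source, that the County Council data can carry diagnoses, and that some patients with serious events will miss visits.

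The scope conflict rests on the text alone. The calendar conflict also rests on training starting at or after inclusion, and it affects only patients included late in October 2017.

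**What to change.** 1. In Secondary outcome measures and in the adverse events paragraph, state that the planned County Council extract will also include diagnoses for hospital contacts due to stroke, other cardiovascular events and fall injuries, and deaths where recorded.
2. Tabulate these by randomised arm for all randomised patients, whether or not they attended the 6- and 12-month assessments. Present this as a supplement to the stated safety population, and say how that population is defined in the no-intervention arm.
3. Cross-check the extract against events reported at visits.
4. Use one scope for adverse events throughout: reconcile the treatment-related wording in Study Endpoints and Secondary outcome measures with the wording that records adverse events and classifies relatedness afterwards.
5. Reconcile the November 2018 end of follow-up and data collection with the 12-month window of patients included late in October 2017.

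The cost is a few diagnosis fields in an extract already planned, one table, a cross-check and some rewording. Ethics approval and consent must cover the diagnosis fields; the document does not say whether they do, so this should be confirmed before the data are requested. One limit remains: falls that do not lead to health care will still depend on what patients report at the visits.

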Inclusion criteria: 1-10 years since stroke onset; able to walk but not independently, i.e. need of manual support or close supervision due to lower extremity paresis, FAC score 2-3 or FAC 4 combined with gait speed <0.8m/s according to 10 meter walk test, which corresponds to limitations in community ambulation (Bowden et al 2008); ability to understand training instructions as well as written and oral study information and to express informed consent or by proxy; body size compatible with the HAL suit.

Exclusion criteria: contracture restricting gait movements at any lower limb joint; cardiovascular or other somatic condition incompatible with intensive gait training; severe, contagious infections (e.g. Methicillin Resistant Staphylococcus Aureus (MRSA) or Extended Spectrum Beta Lactamase bacteria).

*Randomisation*

Randomisation will be performed by a clinician, who is not otherwise involved in the study according to a block design procedure where patients are randomized into each group.

*Interventions*

To standardize the training procedure, training with HAL is performed on a treadmill and to enable body weight support. Body weight support is used to prevent falls and to unburden the weight of the suit (9 kg). The training program is performed by physiotherapists, trained in the HAL method and the study procedures.

The conventional gait training is performed according to current best evidence based practice and may include over ground walking with assistance and/or assistant devices as well as the use of a treadmill and body weight support and training of gait function in activities of daily living

Intensive gait training with HAL is performed 1 session/day, 3 days/week for 6 weeks and each session will not exceed 60 min of effective walking time with HAL. In addition, each session will include conventional gait training that will not exceed 30 min effective training time. At the end of the 6 weeks, the physiotherapist that has been engaged in the patient’s conventional training will perform 1-2 home visits to inform/educate the patient and those who are providing assistance to the patient in how the patient can make use of any gains in gait function during activities of daily living. The 1^st^ control group will receive conventional gait training performed 1 session/day, 3 days/week for 6 weeks that will not exceed 1h 30 min effective training time. The 2nd control group will not receive an intervention.

*Data collection*

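### The set labelled ITT is a modified ITT: its start-of-training condition is undefined for the no-intervention arm and, sensibly read, removes patients from the two training arms only

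*Protocol*

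**What the plan says.** Under Power calculation and statistics, the protocol defines two populations.

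- **All Available-Patients (AAP):** "all randomised patients regardless of further participation will be used to present demographic and baseline characteristics". No other use is given for this set.
- **Intent-to-Treat (ITT):** "all patients, who were randomised and started the intervention program regardless if and when they withdrew". Every efficacy and safety result is to come from this set.

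Under Interventions, the third arm is described in one sentence: "The 2nd control group will not receive an intervention". Data collection repeats this, describing the participants in that arm as those "who are not receiving an intervention, will document any scheduled training sessions in an web based application (app"), with a weekly interview as the alternative.

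Under Study Endpoints, the same arm is part of the primary comparison, which sets side by side "a) intensive training with HAL, b) intensive training without HAL and c) standard training", in their effect "on independence in ambulation after intervention by comparing the Functional Ambulation Category in each group".

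The protocol nowhere says what starting the program means for a patient assigned to the third arm.

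**The concern.** An intention-to-treat set keeps every randomised patient in the assigned arm, so that the arms differ only by chance and by assignment. Adding a condition that is met or failed after allocation gives up that guarantee to the extent that patients fail it.

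Here the condition can also act unequally. Patients know whether they were assigned to exoskeleton training, to conventional training or to nothing; the only blinding described is that of the assessing physiotherapist. The training arms ask for three sessions a week for six weeks, and the third arm asks for none. A patient who declines or falls ill between allocation and the first session leaves the analysis if assigned to training. The same kind of patient assigned to the third arm stays in.

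At stake are the two contrasts with the third arm. The contrast between the two training arms is less exposed, because the same condition applies to both.

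**Working it through.** **1. The planned numbers.** The protocol states: "The study will require 54 (18x3) patients at each study sight, i.e. 162 patients in total". With three sites, 18 × 3 × 3 = 162, which reproduces its total and implies 18 × 3 = 54 per arm. The rest of this check does not depend on how the 18 was derived.

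**2. Apply the set definition to each arm.**

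| Arm | Is there a program to start? | Effect of the start condition |
|---|---|---|
| HAL training | Yes | Non-starters removed |
| Conventional intensive training | Yes | Non-starters removed |
| 2nd control group | None, stated twice | Undefined; sensibly, all kept |

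**3. Set sizes on the sensible reading.** Let d be the share of trainees who never start. The protocol gives no value; it says only that expected loss per arm is minimal. The values below are assumptions. Each training arm contributes 54 × (1 − d), and the third arm contributes 54.

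| d (assumed) | HAL | Conventional | Third arm | Total |
|---|---|---|---|---|
| 0% | 54 | 54 | 54 | 162 |
| 5% | 51.3 | 51.3 | 54 | 156.6 |
| 10% | 48.6 | 48.6 | 54 | 151.2 |
| 15% | 45.9 | 45.9 | 54 | 145.8 |

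Analysing all randomised patients gives 54/54/54 at any d, provided their outcomes are obtained.

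**4. Shift in a training-versus-control contrast.** Let g be the amount by which mean FAC after the intervention period is lower in non-starters than in starters of the same arm. The all-randomised mean of that arm is (1 − d) × starters' mean + d × non-starters' mean. Therefore

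starters' mean − all-randomised mean = d × g.

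The third arm is kept whole, so its mean does not move, and the contrast shifts by d × g.

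| d (assumed) | g (assumed, categories) | Shift (FAC categories) |
|---|---|---|
| 0% | any | 0 |
| 5% | 0.5 | 0.05 × 0.5 = 0.025 |
| 10% | 0.5 | 0.10 × 0.5 = 0.05 |
| 15% | 1.0 | 0.15 × 1.0 = 0.15 |

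Against the one-category difference used in the power calculation, the range is 0.025/1 = 2.5% to 0.15/1 = 15%.

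**5. What d × g contains.** The deficit g mixes two things: non-starters may have a worse prognosis, and they also received no training. Only the first is selection bias. The second is the ordinary dilution that an intention-to-treat comparison accepts. So d × g is the full gap between the analysis as written and a true ITT analysis, and the selection part may be smaller. If g is negative (non-starters do better), the sign reverses.

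**6. HAL versus conventional training.** The shift is d₁g₁ − d₂g₂, with one pair of values for each training arm. It cancels if non-start and deficit are alike in the two arms.

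**The case against.** The case on the other side has real substance, and it rules out several stronger readings.

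- **A reader might infer that the third arm drops out.** Word for word, nobody in that arm starts a program, so 54 of 162 patients (33%) and two of the three contrasts would go. The protocol as a whole does not support this. It puts the arm in the primary comparison, counts it in the sample size and prescribes weekly data collection for it. The wording is a drafting gap, not a planned loss.
- **A reader might infer that third-arm safety events are lost.** That follows only from the same word-for-word reading. The adverse-event text covers the study period and does not restrict documentation by arm.
- **A reader might infer that training is certainly favoured.** The protocol gives neither a non-start rate nor any information on who would not start. It excludes, at entry, conditions incompatible with intensive gait training, which removes one health-related reason for not starting. Non-start for practical reasons could carry no deficit, or one in the other direction. The protocol also expects minimal loss.
- **A third reading exists.** The third arm is elsewhere called standard training or standard care, and it has a log or weekly interview that a patient could be said to start. The condition might then apply to all three arms. The protocol does not say so, and starting a log is a different hurdle from starting a training course. The set would still depend on events after randomisation.

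It could also be said that the definition belongs in a statistical analysis plan. That does not answer the point: the protocol itself fixes the set and assigns it to all efficacy and safety data.

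What stands is narrower than a lost arm or a proven bias. The label is wrong, the entry condition is undefined for one arm, and its most sensible application is unequal between arms.

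**Conclusion.** The point holds as a defect in a stated definition. The set named ITT is a modified ITT, with an entry condition that the 2nd control group cannot meet in any way the protocol describes. Read sensibly, exclusions fall on the two training arms alone, so both contrasts with the third arm can be biased if any trainee does not start.

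The size is not known. The illustration of 0.025–0.15 FAC category in favour of training rests on an assumed 5–15% non-start and an assumed 0.5–1.0 category deficit, neither of which is in the protocol. It is modest beside the planned one-category difference, and it is zero if every trainee starts. The correction is still warranted, because the validity of the primary analysis set should not depend on a non-start rate that nobody has stated, and a better set is already defined in the same section.

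**What to change.** 1. Define ITT as all randomised patients, analysed in the arm assigned, whether or not training began. This is the existing AAP definition with analysis by assigned arm added. Use it for the primary FAC analysis and all efficacy contrasts.
2. Seek the scheduled blinded FAC assessment in patients who never start training.
3. State a safety-set entry rule that explicitly includes the no-intervention arm. Counting all randomised patients from randomisation is one option; an entry rule written for each arm is another.
4. Keep the starters-only set as a labelled sensitivity analysis.

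The cost is a wording change plus follow-up of what should be few patients. Two limits should be acknowledged. Including untrained patients dilutes the estimated effect somewhat. Some non-starters may also decline assessment, so the new definition removes the selection only as far as their outcomes are obtained.

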**New technology for individualised, intensive training of gait after stroke– phase III trials**

**Study II**

**Purpose and aims**

The overall purpose of this project is to establish the added value of training with the Hybrid Assistive Limb (HAL) exoskeleton system as part of regular rehabilitation intervention programs after stroke.

The main specific aims are

1. to demonstrate the effect of intensive training with HAL in comparison with intensive training without HAL and with standard care only, in a later phase (1-10 years) after stroke with regard to gait and cardio-vascular function, activity and participation;
2. to estimate health care utilisation and cost effectiveness of using the HAL during the first year after stroke.

**
[figure not shown]
**

Figure 1. Illustratíon of HAL exoskeleton for gait training on treadmill with Body Weight Support.

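### The protocol sets a blanket 5% level for a three-arm primary FAC comparison and names neither the deciding contrast nor a gate, so familywise error can reach about 9% to 12%

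*Protocol*

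**What the plan says.** Protocol, Purpose and aims, sets out "to demonstrate the effect of intensive training with HAL in comparison with intensive training without HAL and with standard care only". That is two contrasts, both involving HAL.

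Protocol, Methods and procedures, Study Endpoints, gives the primary aim as a comparison of "a) intensive training with HAL, b) intensive training without HAL and c) standard training", assessed "on independence in ambulation after intervention by comparing the Functional Ambulation Category in each group". That covers three groups and singles out no pair.

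Protocol, Power calculation and statistics, sizes the trial on "the expected minimum difference of one category between treatment groups", with "a significance level of 5% and a power of 80" per cent, and does not say which groups. The same section sets the testing rule, "Hypothesis testing will be carried out at the 5% (two-sided) significance level". It then plans median differences between groups with 95% intervals, and for categorical variables generalised linear models giving odds ratios, intervals and p-values judged at 0.05.

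The protocol contains no primary contrast, overall test, testing order or multiplicity adjustment.

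**The concern.** A three-arm comparison offers up to three pairwise contrasts. A single 5% level with no order or gate lets whichever contrast succeeds be presented as the primary result, at a nominal level that does not cover the set.

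The choice of contrast also matters for interpretation. The overall purpose is to establish the added value of HAL, and the section on clinical significance looks to phase III evidence for introducing the device in European care. The second control group receives no intervention, so HAL against that group cannot separate the device from the extra training. HAL against intensive training without HAL can. As written, the two contrasts have equal standing.

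**Working it through.** **The plan's own figure.** 18 per arm per site × 3 arms × 3 sites = 162, so 54 per arm if allocation is equal, as 18x3 implies. The arithmetic is right, but 162 cannot be derived from the stated inputs, because neither an SD nor a dropout figure is given. With n = 2(1.960 + 0.842)² SD²/Δ² and Δ = 1 category, SD = √(n/2)/2.802:

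- 54 per arm: 5.196/2.802 = 1.855.
- 18 per arm: 3/2.802 = 1.07.

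The SD is therefore an assumption in everything about power below. I use 1.0 to 1.855.

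**Familywise error, all three arms equal, each test at 5% two-sided.**

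- Three pairs. At least one is rejected when the range of the three standardised means exceeds 1.960 × √2 = 2.772. The studentised-range tail for three groups is 12.2%, and it is also 12.2% with a pooled t test at 54 per arm. Pairwise Wilcoxon tests on an assumed six-level distribution gave 11.9%. Three independent tests would give 1 − 0.95³ = 14.3%, an upper check.
- Two HAL contrasts. They share the HAL arm, so their correlation is 0.5. 1 − P(|Z₁| < 1.96 and |Z₂| < 1.96) = 9.1%.
- False claim that HAL is better than at least one control. 1 − P(Z₁ < 1.96 and Z₂ < 1.96) = 4.5%. A single two-sided 5% test allows 2.5% in that direction.
- Overall three-arm test first, then pairs at 5%: 5.0%.

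**Why the gate is enough.** With three arms, any two pairwise null hypotheses together imply that all three arms are equal. The overall test is the test of that joint hypothesis. Overall test first, then each pair at full 5%, is therefore a closed procedure. If exactly one arm differs, only one true pairwise null remains, and its error is already 5%.

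**Power cost for HAL versus conventional training.** Difference of one category, 54 per arm, normal approximation. Let z be the pairwise statistic, with mean √27/SD, and w the independent contrast of the third arm with the average of the other two. Without the gate the pair is claimed if |z| > 1.96. With it, z² + w² > 5.99 is needed as well.

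| SD (assumed) | Ungated | Third arm one category below conventional | Third arm equal to conventional | Third arm midway |
|---|---|---|---|---|
| 1.0 | 99.9% | 99.9% | 99.9% | 99.8% |
| 1.2 | 99.1% | 99.1% | 99.0% | 97.8% |
| 1.855 | 80.0% | 80.0% | 75.7% | 69.6% |

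The largest loss is about 1.3 points at SD 1.2, and 80.0 − 69.6 = 10.4 points at SD 1.855. Simulation with pooled t tests agrees at SD 1.855: 79.5% to 75.0% when one arm differs, and 79.4% to 68.7% when the third arm is midway. The midway case is the worst, because the mean of w is then zero. It places the group without intervention above the conventional-training group. If that group is equal to or below conventional training, the loss at SD 1.855 is at most about 4.5 points.

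**The case against.** The strongest objection is that testing order and multiplicity are commonly left to a statistical analysis plan, which is not shown. The sentence on the 5% level is not false in itself, and nothing says that three pairwise tests each count as primary. Comparing FAC in each group could mean one three-group test, and the generalised linear model could supply it, in which case the error is 5%. This stands as a limit: the error rates apply only if each pairwise contrast can carry a primary claim. It does not remove the point. The protocol states a level for all testing, and its two descriptions of the primary comparison imply different sets of contrasts.

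A reader might infer that the chance of a false claim for HAL is 12%. The documents do not support that. The 12.2% counts all three pairs, in either direction, with all arms equal, and includes conventional training against no intervention, which says nothing about HAL. On the wording of the aims the figure is 9.1%, and for a false claim of HAL superiority it is 4.5%. That last figure is below 5%, but the matching rate for one test is 2.5%.

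A reader might also infer that the gate is practically free on the plan's own assumptions. No SD is stated, so the plan cannot show this. If 54 per arm was meant to give exactly 80% power, the SD is 1.855 and the cost can reach roughly 10 points.

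Finally, whether comparisons with two different controls need a joint adjustment is debated. That bears on which family to protect. It does not excuse leaving the deciding contrast unnamed.

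**Conclusion.** The point holds as a gap in what the protocol fixes for its primary comparison. If each pairwise contrast can support a primary claim at 5%, the familywise error with all arms equal is about 9.1% (two HAL contrasts) to 12.2% (three pairs), and a false claim of HAL superiority has probability 4.5% instead of 2.5%. These figures assume equal allocation and approximately normal test statistics, and hardly depend on the SD. The cost of the remedy does depend on it, and on where the third arm lies.

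The conclusion is confined to the protocol shown. It does not follow that the trial will be analysed without error control, nor that every secondary test must be relabelled exploratory, which would go beyond the defect.

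**What to change.** For the primary endpoint, replace the blanket sentence with wording such as: *Post-intervention FAC is first compared across the three arms by an overall test at 5% two-sided. Only if this is significant are the pairwise contrasts tested, each at 5% two-sided. HAL versus intensive training without HAL is the contrast that addresses the added value of HAL.* Align the aims and endpoint sections on whether two or three contrasts belong to the primary family.

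The cost is a short text change and no extra patients. For a one-category HAL versus conventional difference at 54 per arm, the loss of power is about 0 to 1.3 points for SD 1.0 to 1.2, and 0 to roughly 10 points at SD 1.855. The sponsor should state the SD behind 162 so that this range can be narrowed. If the loss is unwelcome, a fixed order that tests HAL versus intensive training without HAL first costs that contrast no power; the other contrasts are then tested only if it succeeds. If an analysis plan already contains a gate or an order, a reference to it in the protocol is enough.
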